## 2.3 Definition of the safety set

The safety set (SAF) includes all randomised patients who have started either IPT-Work or SP group sessions. Treatment cross-overs are impossible to occur due to the logistic arrangements in the trial. Patients are analysed according to the received treatment.

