## 2.4 Estimands: Overview

The following summary and Table 3 give an overview about the definition of the estimands.

Populations:

- FAS, all randomised patients
- SAF, patients who start randomised intervention (treatment cross-overs are impossible to occur due to the logistic arrangements in the trial)

Treatment definition:

- IPT-Work vs SP, as randomised
- AtIPT-Work vs AtSP: as treated, intervention which was started

Intercurrent events:

- Treatment interruptions, treatment discontinuation, prohibited concomitant treatments, non-start (randomised treatment not started)

*Table 3: Overview of Estimands*

| No. | Variable (endpoint) / summary measure                                                    | Treatment          | Population | Intercurrent events |
|-----|------------------------------------------------------------------------------------------|--------------------|------------|---------------------|
| 1   | Relative change in HRSD-24 score from baseline to follow-up / difference of means        | IPT-Work vs SP     | FAS        | All ignored         |
| 2   | Relative change in HRSD-24 score from baseline to end of treatment / difference of means | IPT-Work vs SP     | FAS        | All ignored         |
| 3   | Remission at end of treatment / odds ratio                                               | IPT-Work vs SP     | FAS        | All ignored         |
| 4   | Remission at follow-up / odds ratio                                                      | IPT-Work vs SP     | FAS        | All ignored         |
| 5   | Response at end of treatment / odds ratio                                                | IPT-Work vs SP     | FAS        | All ignored         |
| 6   | Response at follow-up / odds ratio                                                       | IPT-Work vs SP     | FAS        | All ignored         |
|     | Further secondary efficacy endpoints / summary measures to be specified in SAP           | IPT-Work vs SP     | FAS        | All ignored         |
|     | (Serious) adverse events / risk difference                                               | AtIPT-Work vs AtSP | SAF        | Non-start           |

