## **7 Safety monitoring and documentation**

### **7.1 Definition of adverse events (AEs) and serious adverse events (SAEs)**

An AE in this study is defined as any untoward medical occurrence in a patient who has been randomised.

The following adverse events (AEs) will be documented to monitor safety of randomised patients according to one of the following categories (select main category)

- A) Worsening of psychopathological symptoms
- B) Appearance of new psychopathological symptoms

- C) Passive suicidal thoughts
- D) Active suicidal thoughts
- E) AEs related to the patient–therapist relationship
- F) AEs related to personal life
- G) AEs related to occupational life
- H) Other (i.e., non-psychopathological) AEs (e.g. influenza or fractures)

A serious AE (SAE) in this study is defined as any untoward medical occurrence that results in any of the following outcomes:

- Death
- Life-threatening situation (patient is at immediate risk of death)
- Inpatient hospitalisation or prolongation of existing hospitalisation (pre-planned hospitalisations do not have to be considered)
- Persistent or significant disability/incapacity
- Failed suicide attempt
- Other important medical event: An event that does not fit any of the other outcomes above, but may jeopardise the patient and may require medical or surgical intervention (treatment) to prevent one of the other outcomes above.

These definitions are based on a standardised questionnaire already applied in previous psychotherapy trials.

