## 7.2 Documentation of AEs and serious AEs (SAEs)

(Serious) adverse events have to be documented in the eCRF beginning from the date of randomisation and ending with the date of the study end.

The documentation obligation of AEs applies to the study psychotherapist or rater who first became aware of the event.

- Characterisation of the event (see above listed events, in case of “Other AEs”, a diagnosis/symptoms have to be provided, symptoms only if diagnosis not yet available)
- Onset/end date
- Severity (mild to severe)
- Relationship to study procedure
- Serious / non-serious (yes/no; yes, if one of the SAE criteria is met)
- Outcome

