### 10.5.9 Analysis of safety

Adverse events are described by main categories A-H (see section 7.1). The incidences of adverse events will be summarised in the SAF by treatment arm with two-sided 95% confidence intervals based on Wilson scores (without continuity correction) according to method 3 in Newcombe (1998).

The AEs will be displayed in summary tables by treatment as follows:

The total number of AEs, the minimum, maximum and mean number of AEs per patient will be calculated per main category A-H and in total.

The incidence of AEs defined by main categories A-H will be calculated as the number of patients who experienced at least one AE with the respective category A-H in percentage of the total number of patients.

Each table will be produced for the following AE-sets:

- All AEs
- All Serious Adverse Events (SAEs)

Additionally, these tables will be recalculated for AEs with onset during the treatment period and for AEs with onset after the treatment period.

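### Adverse events are recorded for all randomised patients from randomisation, but the planned safety summaries use only those who started group sessions; add tables for all randomised patients and a listing for non-starters

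*Protocol*

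**What the plan says.** Collection covers every randomised patient. Protocol section 7.1 states: "An AE in this study is defined as any untoward medical occurrence in a patient who has been randomised". Section 7.2 requires (serious) adverse events to be "documented in the eCRF beginning from the date of randomisation and ending with the date of the study end".

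Analysis covers a subset. Section 2.3 states: "The safety set (SAF) includes all randomised patients who have started either IPT-Work or SP group sessions". In section 2.4 the safety comparison has its own treatment definition, "AtIPT-Work vs AtSP: as treated, intervention which was started". The (S)AE row of Table 3 gives a risk difference in the SAF and names non-start as the intercurrent event. Section 10.5.9 follows this: "The incidences of adverse events will be summarised in the SAF by treatment arm".

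Non-start is foreseen. Section 2.4 lists it among the intercurrent events, and section 10.5.4 notes that the actual group size can fall below the randomised size when a patient does not begin.

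Section 2.3 also says that treatment cross-overs cannot occur.

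**The concern.** Membership of the SAF depends on something that happens after randomisation and that an adverse event can itself bring about. The AE categories in section 7.1 include worsening symptoms and suicidal thoughts, hospitalisation is an SAE criterion, and section 7.4 links acute suicide risk to inpatient admission. A patient admitted between randomisation and the first session may well not begin group therapy. That patient then leaves both the numerator and the denominator of the arm's incidence because of the event being counted. The same holds for a patient who attends the individual preliminary talk of section 5.3.1, has an event, and never attends a session.

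At stake is the completeness of the reported safety comparison. Serious events are likely to be few, so one omitted patient can visibly change an arm's percentage. The comparison in the SAF is also no longer strictly between the groups as randomised. The trial would already hold the events in its database, yet the protocol names no table or listing that shows them.

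**Working it through.** **1. Populations side by side**

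| Step | Who is covered | Place in the protocol |
|---|---|---|
| AE definition | all randomised | 7.1 |
| AE/SAE recording | all randomised, from randomisation to study end | 7.2 |
| (S)AE risk difference | randomised and started (SAF) | 2.4, Table 3 |
| AE incidences with Wilson intervals | SAF | 10.5.9 |
| Efficacy (FAS) | all randomised | 2.1 |

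Section 10.5.9 names the SAF for the incidences and does not repeat it for the tables of AE counts, but the Table 3 row assigns (S)AEs as a whole to the SAF. Since cross-overs are ruled out, the FAS by randomised arm and the SAF as treated differ only by the non-starters.

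**2. Length of the window.** In Table 5 randomisation is at W0 and the first treatment visit at W1 (± 4 days), and follow-up ends at W21. The gap is about 1/21 = 4.8% of the observation time after randomisation.

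**3. How many patients (assumption).** The protocol gives no non-start rate. Section 1.2 reports no dropouts in the pilot, so zero is possible, and then nothing is lost. Assuming 2% to 5% non-starters among the 144 patients of section 3.3: 144 × 0.02 = 2.9 and 144 × 0.05 = 7.2, so about 3 to 7 patients outside the SAF. Only those with an event affect a numerator.

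**4. Effect on one arm's SAE incidence (assumed counts).** Section 3.3 gives about 72 patients per arm. Section 10.5.9 names the Wilson interval without continuity correction, with p = x/n and z = 1.96:

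centre = (p + z²/2n)/(1 + z²/n); half-width = z·√[p(1 − p)/n + z²/4n²]/(1 + z²/n)

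| Assumed situation in one arm | All randomised | SAF |
|---|---|---|
| 2 SAE patients; 1 of them is the only non-starter | 2/72 = 2.8% (0.8 to 9.6) | 1/71 = 1.4% (0.2 to 7.6) |
| 3 SAE patients; 1 of them is the only non-starter | 3/72 = 4.2% (1.4 to 11.5) | 2/71 = 2.8% (0.8 to 9.7) |
| 3 SAE patients; 4 non-starters, 1 with an SAE | 3/72 = 4.2% (1.4 to 11.5) | 2/68 = 2.9% (0.8 to 10.1) |
| 3 SAE patients; 4 non-starters, 2 with an SAE | 3/72 = 4.2% (1.4 to 11.5) | 1/68 = 1.5% (0.3 to 7.9) |

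If the other arm also had 2/72 and no non-starters, the first row would move the risk difference from 0 to 1.4% − 2.8% = −1.4 percentage points. A single non-starter without an SAE changes almost nothing: 2/72 = 2.78% against 2/71 = 2.82%.

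**5. What is unaffected.** Sample size, power and the significance level do not depend on the safety set.

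**The case against.** The strongest reply is that this is a declared choice. Safety has its own row in Table 3, as treated, with non-start named, and a safety set of patients who started treatment is conventional. Recording more widely than one analyses is not a contradiction. That stands: the SAF is not an error, and its definition need not change.

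A reader might infer that serious events disappear. The documents do not support this. The events stay in the eCRF (7.2) and, if serious, on the SAE form (7.3). Section 11 has the DSMB informed of observed adverse events without restriction to the SAF. Sections 10.5.2 and 10.5.4 make non-starters visible through the CONSORT flow chart and the group sizes. The omission concerns the planned summaries only.

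A reader might also infer that the period tables lose events between randomisation and session 1 even in patients who start. Section 10.5.9 plans tables for "AEs with onset during the treatment period and for AEs with onset after the treatment period", but these come in addition to the tables of all AEs and all SAEs, which contain every event in a starter. The protocol does not define when the treatment period begins, and Table 5 puts the preliminary talk in a treatment column (V2). This is an undefined boundary and not a separate error.

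Nor do the documents show that non-start would differ between arms because of adverse events. Patients are unblinded and the control is not work-directed, so it is possible, but nothing establishes it. The halving in the first row of the table is likewise not an expected result: it puts one of two SAEs in a window of about one week out of 21, and the two intervals overlap almost entirely.

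Finally, the SAP is not at hand and may add a listing. That tempers the point but does not remove it, because the protocol itself already fixes the set and the tables.

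**Conclusion.** The point holds as a limited mismatch between collection and analysis. Events in randomised patients who never start group sessions are recorded but are missing from the (S)AE risk difference and the AE incidences, and the protocol plans nothing that recovers them. The likely number is small. The illustrations show that one omitted SAE patient can move an arm's percentage by about 1.4 points, but they rest on assumed SAE and non-start counts. Safety is descriptive (2.2.2, 10.5.1), so no confirmatory conclusion changes. This is an inexpensive improvement to the reporting and not a flaw that threatens the trial.

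**What to change.** Keep the SAF and the Table 3 safety row as declared. In section 10.5.9, add:

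- the AE and SAE incidence tables for all randomised patients (FAS) by randomised arm, with the same Wilson intervals;
- a listing of AEs and SAEs in randomised patients who did not start group sessions, by arm, with onset date.

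The cost is one repeated set of tables and one listing from data already collected. There are two downsides to state alongside the added tables. Non-starters miss the session visits, where section 5.3.1 has therapists prompt for adverse events, so their events are less fully ascertained and including them can dilute the incidence. Some events that cannot be due to group sessions will also be counted. Showing the SAF and FAS tables together, with the listing, lets the reader see both effects.

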## 2.4 Estimands: Overview

The following summary and Table 3 give an overview about the definition of the estimands.

Populations:

- FAS, all randomised patients
- SAF, patients who start randomised intervention (treatment cross-overs are impossible to occur due to the logistic arrangements in the trial)

Treatment definition:

- IPT-Work vs SP, as randomised
- AtIPT-Work vs AtSP: as treated, intervention which was started

Intercurrent events:

- Treatment interruptions, treatment discontinuation, prohibited concomitant treatments, non-start (randomised treatment not started)

*Table 3: Overview of Estimands*

| No. | Variable (endpoint) / summary measure                                                    | Treatment          | Population | Intercurrent events |
|-----|------------------------------------------------------------------------------------------|--------------------|------------|---------------------|
| 1   | Relative change in HRSD-24 score from baseline to follow-up / difference of means        | IPT-Work vs SP     | FAS        | All ignored         |
| 2   | Relative change in HRSD-24 score from baseline to end of treatment / difference of means | IPT-Work vs SP     | FAS        | All ignored         |
| 3   | Remission at end of treatment / odds ratio                                               | IPT-Work vs SP     | FAS        | All ignored         |
| 4   | Remission at follow-up / odds ratio                                                      | IPT-Work vs SP     | FAS        | All ignored         |
| 5   | Response at end of treatment / odds ratio                                                | IPT-Work vs SP     | FAS        | All ignored         |
| 6   | Response at follow-up / odds ratio                                                       | IPT-Work vs SP     | FAS        | All ignored         |
|     | Further secondary efficacy endpoints / summary measures to be specified in SAP           | IPT-Work vs SP     | FAS        | All ignored         |
|     | (Serious) adverse events / risk difference                                               | AtIPT-Work vs AtSP | SAF        | Non-start           |

### 3 Study Plan

#### 3.1 Study Design

[figure not shown]

Figure 1: Study Design

Table 4: Timetable for the Study

|                                          |                              |
|------------------------------------------|------------------------------|
| Informed Consent of first patient (FPFV) | 1 st quarter 2025 |
| Randomisation of last patient            | 4 th quarter 2026 |
| End of trial for last patient (LPLV)     | 1 st quarter 2027 |
| Statistical analysis                     | 2 nd quarter 2027 |
| Treatment duration per patient           | 2 months                     |

#### 3.2 Participating Centres

6 centres in Germany (2x Freiburg, Mannheim, Frankfurt am Main, Rosenheim/Prien and Hannover), which meet the structural and personnel requirements for performing the planned regular study-related investigations, have been selected and initiated to carry out the trial:

- Department of Psychiatry and Psychotherapy, Medical Center - University of Freiburg (PI: [name] [name])
- Department of Psychosomatics, Medical Center - University of Freiburg (PI: [name] [name])
- Department of Psychiatry and Psychotherapy, Central Institute of Mental Health, Medical Faculty Mannheim, University of Heidelberg (PI: [name] [name])
- Department of Psychiatry, Social Psychiatry and Psychotherapy, Hannover Medical School (PI: [name] [name])

- Department of Psychiatry, Psychosomatic Medicine and Psychotherapy, University Hospital Frankfurt – Goethe University Frankfurt (PI: [name] [name])
- Schoen Clinic Roseneck, Prien am Chiemsee (PI: [name] [name])

Qualifications were evaluated using self-report questionnaires, including patient numbers from previous years, and were checked by a monitor. If necessary, additional qualified centres can be included in the course of the study.

### **3.3 Number of Study Participants**

A target sample size of 144 patients will be enrolled in the study, about 72 in each of the two trial arms. Therefore, about 190 patients will be assessed for eligibility.

### **3.4 Methods against bias**

For logistical reasons, clusters of 4-6 eligible patients at a time will be randomised to group psychotherapy according to the IPT-Work or SP condition. To avoid selection bias, the raters who identify eligible patients and obtain informed consent will not be informed about the randomisation result, nor about ongoing or previous IPT-Work or SP psychotherapy groups at their respective centre.

To further avoid selection bias, the randomisation code to allocate patient groups to interventions will be generated by the CTU using the following procedure to ensure that treatment assignment is unbiased and concealed from patients and site staff. Randomisation of patient groups will be performed, stratified by centre, in blocks of variable length with a 1:1 ratio. The block lengths will be documented separately and will not be disclosed to the centres. The randomisation code will be produced by validated programmes based on the Statistical Analysis System (SAS).

Obviously, blinding of patients and study psychotherapists performing the interventions is not possible. However, data acquisition other than patient reported outcomes will be done by trained blinded clinical raters not involved in patient management. Each site will implement procedures to mask patient treatment assignment from the clinical rater by reminding the patients at each visit not to mention anything that might reveal their treatment condition. Diagnostic training of raters in the SCID-5, HRSD-24 and (S)AE assessments will be conducted by expert trainers and interrater reliability will be ensured. The other measures are self-rated in a standardised questionnaire format.

All confirmatory analyses are fully specified in the trial protocol to avoid reporting bias. The trial is registered prospectively at the German Clinical Trials Register (see chapter 13), and its results will be published irrespective of the outcome to prevent publication bias.

### **3.5 Roles and Responsibilities**

#### **3.5.1 Coordinating investigator**

[name] as the coordinating investigator (CI) is the lead researcher responsible for the overall conduct of this study. The CI oversees the trial's design, implementation, and adherence to ethical and regulatory standards. She facilitates communication among the study sites, manages the data collection process, and ensures the study progresses according to the protocol. The CI also serves as the primary point of contact for regulatory bodies and sponsors.

### **3.5.2 Principal investigators at the sites**

Principal Investigators (PIs) at the sites are the lead researchers at each participating location. They are responsible for the implementation of the study protocol at their respective sites, including the recruitment and management of participants, ensuring compliance with the study's procedures, and overseeing data collection. The PIs communicate with the Coordinating Investigator to report on progress and any issues that arise during the trial.

### **3.5.3 Rater**

Raters evaluate participants' mental health status, symptoms, and progress using standardised instruments. All raters have at least a B.Sc. in Psychology (or comparable) and are trained in a 2-day training to assess study participants based on predefined criteria and measurement tools. They are crucial for maintaining the reliability and validity of the outcomes by providing unbiased assessments. Therefore, raters will remain blind to the participants' group assignments whenever possible to reduce bias in their evaluations (for details see 5.4.1). To ensure adherence and interrater reliability, raters will independently rate videos of HRSD-24 goldstandard ratings (primary outcome) during the training and the study duration.

### **3.5.4 Psychotherapists**

Study psychotherapists are in a completed or far advanced stage of psychotherapy training. All therapists will execute IPT-Work as well as SP groups after thorough training to ensure a high treatment quality (2-day training course in presence in each IPT-Work and SP followed by 3 half-day online booster workshops after the start of the group therapies app. every 6 months). All trainings are led by clinical experts in the field ([name], [name], [name], [name], [name] or others delegated by the CI). Study therapists will be intensely instructed and trained to adhere to the manual of each condition and not to mix the intervention types. To check for adherence and to support the supervision, a 'Therapeutic Element Checklist' (Stundenbogen) for IPT-Work (e.g. strategies for addressing work-life-balance, demand-control-balance, effort-reward-balance, and work as a social role) and SP (e.g. reflective listening, facilitation of affect, helping the patient to feel understood) is filled out by the therapist immediately after each group session. Separate supervisors ([name], [name] or others delegated by the CI) for each treatment arm will review the 'Therapeutic Element Checklist' regularly in ongoing supervision. Every second or third session will be supervised by the responsible supervisors (who also conducted the IPT-Work and SP trainings, respectively) in biweekly video conference meetings. Furthermore, a diagnostic training of raters in SCID-5 and HRSD-24 will be conducted in presence ([name], [name], [name] or others delegated by the CI), and interrater reliability will be ensured.

## **4 Subject Population and Selection Criteria**

According to the recruitment strategy individuals working in firms, institutions (such as clinics, schools, universities), also from outpatient centres and private practices (primary care, psychosomatics, or psychiatry), and media recruited participants will be enrolled in the IPT study. In order to fulfil the recruitment rates within the planned timeframe, sites will be provided with the best possible support finding and recruiting patients into the trial. The recruitment procedure for this randomized controlled trial (RCT) is based on the successful procedure of our pilot study. There, the recruitment process proved to be effective, even under more demanding conditions. Specifically, the pilot study required a larger sample size per centre (n=28), and participants in both groups had to be randomized simultaneously. Despite these challenges, we were able to recruit participants within the planned timeframe. This experience underscores the feasibility and

robustness of our recruitment strategy, which has been slightly refined for the current RCT to further enhance its efficiency. In current practice, respective patients are often not evaluated for depression. Hence, a maximum effort is put to exposure of the targeted patient group to the study sites. To do so, a study website is created to provide checklists, newsletters, and flyers, information about patient informed consent aspects, and letters for resident physicians, etc.

As the general public often regards psychotherapy with or without medication as the preferred treatment option, we will provide corresponding information for treating physicians.

